#### The problem-solving intervention

The intervention focuses on the individual and the involvement of the workplace [11, 29] in addition to CAU [3]. The added value on top of CAU is the intervention’s problem-solving process and the coordination by the RC between the employee on sick leave, his/her employer and the health care professionals.

Communication between the employee, the RC and the employer is needed for making an inventory of problems, opportunities and identifying the help needed to solve the problems [11]. The present intervention is a modified version of the Dutch sharp-at-work intervention [29] which aimed to prevent recurrence of sick leave among employees with CMDs who had returned to work. The Dutch target group differed from the target group of the present study, i.e. persons on sick leave. The new, adapted intervention is a five-step problem-solving process which aims to identify and find possible solutions to problems perceived as obstructing the RTW process (Fig. 2). A meeting with the person on sick leave, his/her employer and the RC is included in the process, as previous research has stressed the importance of communication between the different stakeholders [30]. The intervention comprises the following five steps:Making an inventory of problems and/or opportunities related to RTW; a collaborative approach involving employee and RC; employer and RC.Brainstorming about solutions, involving employee and RC.Writing down solutions, identifying the support needed to implement them and assessing their applicability, involving employee and RC.A meeting with the person on sick leave, the employer and the RC to discuss solutions and make an action plan, involving employee, RC and employer.Evaluation of the action plan and implementation of solutions, involving employee and RC.

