### Care as usual (CAU)

The RCs in the control condition will continue to deliver CAU during the study period. CAU may include strategies for the RTW process and may involve the employer. However, the strategies used by the RCs to date are not structured in the same way as in the intervention condition, and do not follow an explicitly stated guidance by problem-solving therapy.

CAU involves cognitive behavioral therapy or medical treatment, or a combination of both [3], as well as the coordination of RTW (meeting with a RC). We will make no specific attempts to ensure that the physicians follow the guidelines for the treatment of CMDs [3]. The participants, their physicians and, if relevant, their psychologists, will not receive any information from the project group about the problem-solving intervention.

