### Process evaluation

As recommended by Moore GF*,* et al. [45], a process evaluation will be conducted. The process evaluation [46] will examine (1) the study’s fidelity, i.e. whether and to what extent it is possible to implement the intervention according to the protocol, (2) reach, dose delivered and dose received, i.e. the relationship between the key elements of the intervention and the effect outcome, and (3) the study’s context, i.e. how the RCs, the persons on sick leave, their employers, their physicians and other stakeholders (e.g. occupational health service, social insurance agency officer) perceive the intervention and the obstacles and enablers which influence the implementation. Process-evaluation data will be collected by means of questionnaires, employees’ medical records and individual interviews with RCs, employees and their employers.

*Fidelity* will be measured by a questionnaire containing questions about whether the intervention was delivered as planned. The RCs in the intervention group will report overall adherence to the manual/fidelity to the method for each employee during the study, after the employee has participated in the problem-solving process. *Reach* is measured for RCs and employees. The RCs participation in the two-day training course will be assessed by attendance and their satisfaction with the course. Eligibility will be screened by medical records, while reach will be assessed as those who are willing to participate in the study. *Dose delivered* will be assessed by means of a questionnaire for the RCs which asks questions about the frequency of face-to-face meetings with the employee, number of telephone follow-ups and the frequency and quality of the three-party meetings with the employer. *Dose received* is defined as the whether or not the participants receive the problem-solving intervention. Dose received will be measured by how much of the intervention that the participants received; number of sessions with the RC; how much the participants were exposed to the different components of the intervention. The content and fulfillment of the recommended follow-ups with the employees will be addressed. The RCs in the control group will receive a check list which helps them to report the content in the control condition.

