#### Blinding

This study has a cluster-randomization design, in which the employees follow the RCs at the PCCs and are randomized before they give informed consent. The employees in both the intervention and the control group receive the same information about the study to equalize employees’ expectations about their participation in the study. The employees are blinded for the treatment allocation since they receive no information about the other group. The RCs are instructed not to tell employees that the study consists of two groups, to ensure that the employees are not aware about the two conditions. The RCs are not blinded for treatment allocation because the RCs in the intervention arm will know that they will receive education and training. An independent statistician will perform the analyses and will be blinded for participant allocation.

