#### Data analysis

Statistical analyses adapted for cluster-randomized controlled trials will be conducted. Linear and generalized linear models will be used. Intention-to-treat analyses and, if relevant, per-protocol analyses will be conducted. Potential confounders will be adjusted for in the analyses, if they prove to be unevenly distributed and might be expected to have an impact on the outcomes when the intervention is compared with the control condition. Possible interaction effects on the primary and secondary outcomes for (1) gender x treatment, and (2) number of sessions with RC x treatment will be assessed. If they are statistically significant, appropriate analyses will be considered. Data collected from interviews and focus groups will be analyzed by methods adapted for qualitative data and normative analysis (cf. [48, 52, 53]).

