##### Statistical power

We estimate that the study population needs to be 220 participants: 110 participants in the intervention and the control group respectively. The participants will be obtained by sampling 10 clusters with 11 participants each in the intervention group and the same number of clusters and participants in the control group. With these numbers it will be possible to achieve around 80% power to detect a difference between the groups of at least 20% of registered sickness absence 18 months after baseline. The intra-cluster correlation was set to 0.010. This sample size calculation is relevant for statistical analyses that take into account a correction factor for the effect of a clustered design and use an alpha level of 0.05.

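### Number of coordinator sessions arises after randomisation, so testing it by treatment as an effect modifier can show an interaction where none exists

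*Protocol article*

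**What the plan says.** In the Data analysis section of the protocol article, the main approach is stated as "Intention-to-treat analyses and, if relevant, per-protocol analyses will be conducted". After a sentence on confounder adjustment, the section names two possible interactions to be examined for the primary and secondary outcomes. One is gender by treatment. For the other the text reads "2) number of sessions with RC x treatment will be assessed". The next sentence sets the consequence for both: "If they are statistically significant, appropriate analyses will be considered".

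Other sections show what kind of variable the session count is:

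- **Process evaluation:** "Dose received will be measured by how much of the intervention that the participants received; number of sessions with the RC". Sessions are a measure of dose received.
- **Blinding:** employees follow their RC's allocation and "are randomized before they give informed consent".
- **The problem-solving intervention:** "The new, adapted intervention is a five-step problem-solving process", so contacts in that arm follow a set sequence.
- **Care as usual (CAU):** usual care covers clinical treatment "as well as the coordination of RTW (meeting with a RC"; the RC's strategies there are described as not structured in the same way.
- **Primary outcome:** sick leave days are counted from baseline to 18 months.

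**The concern.** A treatment-by-covariate interaction has a causal reading when the covariate is fixed before allocation. Gender meets that condition and session count does not. The plan treats the two alike.

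Three features matter here. First, the arm shapes the count: a five-step process in one arm, unstructured RC meetings in the other. People with, say, three sessions are therefore differently selected in each arm. Second, sessions fall inside the period over which the outcome is counted, so a person who stays on leave longer has more opportunity for sessions. Third, nothing in the article suggests that the relation between sessions and prognosis is the same in both arms.

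A false positive could be read as showing that the intervention works only with enough sessions, or the reverse. The Discussion says the knowledge gained will form the basis for implementation. Significance is also the stated trigger for further analyses that are not specified.

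**Working it through.** **Inputs from the article (Statistical power).** "220 participants: 110 participants in the intervention and the control group respectively"; 10 clusters of 11 per arm; intra-cluster correlation 0.010; alpha 0.05 (two-sided assumed); about 80% power for a 20% difference. The article gives no figure for the interaction analysis.

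**The plan's own figure.** Design effect = 1 + (11 − 1) × 0.010 = 1.10, so the effective size is 110 / 1.10 = 100 per arm. The detectable standardised difference at 80% power is (1.960 + 0.842) × √(2/100) = 0.396. A 20% relative difference then needs a coefficient of variation of 0.20 / 0.396 = 0.505. No SD or control level is given, so the 80% is attainable but cannot be strictly reproduced.

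**Null simulation.** 4,000 trials per setting, 20 clusters of 11, with no effect of treatment or sessions on the outcome. Assumed values: mean 150 days and SD 75 (coefficient of variation 0.5, in line with the step above); a latent prognosis U explaining half of the within-cluster variance; sessions Poisson with arm mean μ and log-slope b on U. The model was linear with treatment, sessions centred at the overall mean, and their product; cluster-robust errors; t with 18 degrees of freedom.

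**Closed form for the expected bias.** Within an arm, Cov(Y, S) = 75 × √(0.99 × 0.5) × bμ = 52.77 bμ and Var(S) = μ + μ²(exp(b²) − 1). The spurious slope of days on sessions is therefore

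β = 52.77 b / [1 + μ(exp(b²) − 1)].

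The expected interaction is β₁ − β₀ (1 = intervention, 0 = CAU). The expected treatment term at mean sessions is −(β₀ + β₁)(μ₁ − μ₀)/2.

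Worked case, μ₀ = 1.5, μ₁ = 4, b₀ = 0.6, b₁ = 0.2:

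- β₀ = 31.66 / (1 + 1.5 × 0.4333) = 19.19
- β₁ = 10.55 / (1 + 4 × 0.0408) = 9.07
- interaction = 9.07 − 19.19 = −10.1 days per session (simulated −10.2)
- treatment term = −(19.19 + 9.07) × 1.25 = −35.3 days (simulated −35.9)

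**Simulated results; the true effect is zero in every row.**

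| Mean sessions CAU / interv. | Log-slope CAU / interv. | Interaction rejected | Treatment term at mean sessions | Treatment term rejected | ITT without sessions rejected |
|---|---|---|---|---|---|
| 1.5 / 4 | 0 / 0 | 6.0% | 0.2 days | 6.2% | 5.8% |
| 2 / 2 | 0.4 / 0.4 | 6.1% | 0.0 | 5.8% | 5.7% |
| 1.5 / 4 | 0.4 / 0.4 | 13.7% | −36.4 | 82.3% | 5.2% |
| 1.5 / 3 | 0.2 / 0.1 | 12.6% | −11.3 | 16.2% | 5.2% |
| 1.5 / 4 | 0.6 / 0.2 | 48.1% | −35.9 | 82.8% | 5.4% |
| 2 / 2 | 0.5 / 0 | 75.2% | 0.0 | 6.1% | 5.7% |
| 1.5 / 4 | 0.6 / 0 | 92.1% | −24.3 | 48.2% | 5.7% |

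Against the SD of 75, −11.3 days is −0.15 SD and −36.4 days is −0.49 SD. Two further settings with slopes of opposite sign gave false interactions in 97% and almost 100% of trials; I put less weight on those.

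**Second set of assumptions.** 110 independent participants per arm; severity related to sessions only in the intervention arm (session means exp(1.1 + sU) against exp(0.3)); outcome related to severity with coefficient 0.5 or 0.7. For s of 0.3 to 0.5 the interaction was rejected in 22% to 52% of trials, against 5.0% at s = 0. The treatment term at mean sessions was −0.10 to −0.19 SD.

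**What drives each error.** A false interaction needs β to differ between arms. Different log-slopes produce that; so can equal log-slopes with different session means (third row). A false treatment term needs sessions to be prognostic and their means to differ. Longer leave itself producing more sessions was not modelled.

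**The case against.** The main trial result does not depend on this test. Intention-to-treat comes first, the interactions are only possible effects to be assessed, and nothing says that the treatment coefficient from the sessions model is the trial's estimate. This stands: without sessions in the model, the rejection rate was 5.1% to 5.8% in all settings, with bias near zero. A reader might infer that the randomised comparison itself is compromised. The article does not support that.

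The size is assumption-driven, and this also stands. The article gives no session counts and no relation between sessions and prognosis. It does not settle which arm would have the steeper slope either; the structured intervention and unstructured usual care suggest, if anything, the steeper one in CAU. A reader might also take the uncentred treatment coefficient, −0.36 to −0.60 SD under the second set of assumptions, as the bias, and compare it with a 0.40 SD effect for which the trial is sized. That coefficient is the contrast at zero sessions, in an arm averaging about three. The article states no standardised effect; 0.396 is back-calculated.

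It may be said that this is exploratory, or left to the analysis plan. The article does not call it exploratory. It places the test among the effectiveness analyses for the primary and secondary outcomes. Details of the follow-up analyses could well sit elsewhere, but the choice of modifier is made here.

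Dose and outcome is a legitimate question, and the Process evaluation and Discussion sections raise it. That supports placing it there, as description, and does not support a between-arm interaction test.

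**Conclusion.** The point holds for the sessions-by-treatment analysis and should be fixed. It does not threaten the primary intention-to-treat comparison or the gender-by-treatment test.

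Under a complete null and non-negative session-prognosis slopes that differ between arms, the interaction was falsely significant in about 13% to 92% of trials. It stayed near 6% when sessions were unrelated to prognosis, or when slopes and session means were both equal. Where session means differed, the treatment term at mean sessions was off by roughly −0.1 to −0.5 SD; with equal means it was not biased. The sizes rest on assumed slopes, session means and outcome SD. That bias can occur follows from the variable being post-randomisation and differently generated in the two arms, both of which the article shows.

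**What to change.** In the Data analysis section, delete number of sessions by treatment from the planned interactions and keep gender by treatment. In the Process evaluation section, state that number of sessions will be described in relation to outcome within the intervention arm only, as an exploratory and non-causal dose description.

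If the effect of receiving the intervention is wanted, a randomisation-based complier-average causal effect that respects clustering can be added as an option. Receipt should be defined as receiving the problem-solving intervention rather than as meeting an RC, because CAU includes RC meetings. The exclusion restriction and other assumptions should be stated.

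The change is to wording; the dose data are already planned. The price is losing a between-arm dose test, which could not be read causally as it stands.

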##### Statistical power

We estimate that the study population needs to be 220 participants: 110 participants in the intervention and the control group respectively. The participants will be obtained by sampling 10 clusters with 11 participants each in the intervention group and the same number of clusters and participants in the control group. With these numbers it will be possible to achieve around 80% power to detect a difference between the groups of at least 20% of registered sickness absence 18 months after baseline. The intra-cluster correlation was set to 0.010. This sample size calculation is relevant for statistical analyses that take into account a correction factor for the effect of a clustered design and use an alpha level of 0.05.

## Discussion

The study is designed as a pragmatic, effectiveness trial that will investigate whether employees on sick leave will benefit from a problem-solving intervention delivered by RCs in primary health care. Analyses will be performed to examine whether the problem-solving intervention has been more successful in reducing sick leave than CAU. In a parallel process evaluation, the RCs’ adherence to the protocol and how treatment fidelity, dose delivered and dose received might influence the sickness absence outcome will be investigated. Furthermore, the process evaluation will increase our understanding of the obstacles to and facilitators of the intervention, contextual factors and the experience of taking part in the intervention. The economic evaluation will examine the intervention’s economic impact on society and the health care system that is expected to deliver the intervention if it is successful. In a health care system guided by and founded on ethical values and norms, it will be essential to relate to, and have strategies for how to handle identified ethical challenges. This knowledge will form the basis for future implementation of the problem-solving intervention in primary health care.

### Methodological considerations

The cluster-randomization, in which the RCs are randomized to intervention and control groups, reduces the risk of contaminating the employees who participate in the study. The RCs will only provide the problem-solving intervention or CAU. Another strength of the study is that participants will be selected by a project assistant who screens medical records for eligible employees on sick leave. The project assistant will have no previous knowledge about the participants or the randomization, thereby reducing the risk of selection bias.

In the Swedish social insurance system, the employer usually pays for sick leave up to and including day 14. The MiDAS register therefore contains sick leave data from day 15 of sick leave. Since short-term sick leave may predict future long-term sick leave, valuable information about short-term sick leave will be collected from the employees. However, with self-reported questionnaires there is always a risk of recall bias and drop-out. The use of text messages facilitates repeated measurements with short recall periods, while the questionnaires are administered at baseline and at 6 and 12-month follow-up. The 6 and 12-month follow-ups may increase the risk of recall bias, but this risk has to be weighed against the frequency of the questionnaires that the participants have to fill in.

The data collected in the process evaluation will be analyzed before the primary and secondary outcomes in the effectiveness evaluation are known to the research group, to prevent biasing interpretations of the intervention’s effectiveness. One of the strengths of the proposed method for the economic evaluation will be its use of comprehensive individual-level data collected for administrative purposes, on both direct and indirect costs. A strength of the proposed methodology for ethical analysis is it context-sensitivity in relation to the Swedish health care system and its inherent ethical values and norms. However, ethical analysis is, on top of demands for internal consistency, dependent upon being critically examined and acknowledged as relevant by the stakeholders. Hence, dialogue concerning this analysis is crucial.

### Possible impact of results

Sick leave due to CMDs is a matter of national and international concern, not only for the individuals themselves but also for their employers and society at large. The costs of sick leave for society are high. Consequently, finding interventions that reduce these costs as well as the human suffering represents cost effectiveness for society and employers and greater well-being for individuals. Moreover, previous economic evaluations of the problem-solving intervention have shown ambiguous results with regards to its cost/effect balance. Costs are furthermore known to differ between countries, based on e.g. the financing of the health care systems. Thus, there is a need for more thorough examination of the intervention’s economic impact. Improved work ability and worker health will be beneficial for individuals, their employers, enterprises, organizations and society at large. The ethical analysis will identify ethical challenges and obstacles but also ethical advantages with the intervention, and thereby provide basis to assess how the intervention relates to the value basis of the Swedish health care and welfare system. In a health care system, where new interventions are constantly introduced, such analyses are essential to understand how the intervention fits into these value systems. If the intervention shows promising results for RTW and work ability, there are good prospects for being able to implement and disseminate it in the primary health care service, which may result in positive effects for society at large (e.g. lower costs for sick leave and rehabilitation).

## Abbreviations

CAU: Care-as-usual
CMDs: Common mental disorders
HRQoL: Health-related quality of life
LISA: Longitudinal integration database for health insurance and labor market studies
MiDAS Micro: Data for the Analysis of Social Insurance
PCC: Primary health care center
RC: Rehabilitation coordinator
RTW: Return-to-work
